### Pain assessment in neonates

Clinical pain assessment in neonates, particularly those delivered preterm, is highly challenging [4, 23]. In the clinical setting, their pain responses have to be observed and assessed using behavioral and physiological indicators, which can vary across premature infants depending on their physiological and neurological development stages [23]. Behavioral indicators used as pain assessment tools include body movements, facial expressions and crying [24]. Some pain assessments also include behavior status indicators, e.g., sleep-wake state [25, 26]. Physiological responses to pain include, for instance, changes in heart rate, respiratory rate, blood pressure, oxygen saturation, vagal tone, and peripheral blood flow [25, 27]. Recently, researchers have begun to investigate more objective approaches to pain assessment, such as measurement of heart rate variability, skin conductance and cortisol as a biomarker of stress [23, 25]. To better understand and assess neonatal pain responses at cortical level, newer brain-oriented techniques, such as electroencephalography (EEG) [28, 29] and functional magnetic resonance imaging (fMRI) [30, 31], are used [11, 32–34]. However, for systematic clinical pain assessment, exclusively observable indicators need to be considered.

Because of the complex nature of pain, multidimensional pain measures that include behavioral and physiological indicators are generally assumed to be most appropriate for the clinical setting [23]. Although most infants show both types of pain response indicators, the correlation between these two indicators is often low [25, 35]. Moreover, no consistent associations between behavioral, physiological and cortical measures of pain have been detected so far [36]. In the face of inconclusive associations between different indicators of pain, the validity of existing multidimensional tools and their choices of indicators are currently being questioned, and, to date, no universally accepted gold standard exists for neonatal pain assessment [23].

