### The Bernese pain scale for neonates

The Bernese Pain Scale for Neonates (BPSN; [41]) was developed by nurses of the University Hospital of Berne primarily for clinical use. Since its development in 1996, it has been widely used for bedside pain assessment in NICUs in the German speaking areas of Europe. Several hospitals in Switzerland have fully integrated the BPSN into their daily routine.

The BPSN is a 9-item multidimensional pain assessment tool that includes behavioral and physiological indicators. The instrument consists of seven subjective (alertness, crying, consolation, skin color, facial expression, posture, and changes in respiratory rate) and two physiological (i.e. objective) (changes in heart rate and oxygen saturation) indicators. Each item is rated on a four point Likert scale (0, 1, 2, and 3). Higher scores indicate greater pain-related distress, and a total score of 11 or higher is considered to indicate pain.

In the year 2004, the BPSN was validated to differentiate between pain and non-pain status in neonates between 27 and 41 weeks of gestation [41]. The results suggested that the BPSN is a valid and reliable pain assessment instrument for assessing acute pain in term and preterm neonates. A shortcoming of this first validation study of the BPSN is the small study population of 12 infants. Furthermore, increasing evidence indicates that pain reactions of neonates are probably influenced by more than noxious stimulation alone; individual contextual factors might also impact pain reactivity [40, 42–44]. Currently, the BPSN focuses entirely on physiological and behavioral indicators.

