### Measures

To establish concurrent validity, neonates’ pain expression is measured by the BPSN [41] and the PIPP-R [26]. The BPSN measures 9 indicators. The two physiological indicators will be captured on an ongoing basis from the neonate’s routine continuous monitoring records (heart rate and oxygen saturation) during the video recording. The six subjective indicators (sleeping state, crying, consolation, skin color, facial expression, posture, and breathing) will be rated by five independent and blinded video raters on a 4 point Likert scale. The raters are blinded towards the phase of the video sequence they are looking at (baseline, heel stick, and recovery). The PIPP-R, which is widely used in North America for assessing acute pain in neonates, measures five indicators of which two are physiological (heart rate and oxygen saturation). The three behavioral indicators (brow bulge, eye squeeze, and naso-labial furrow) will also be assessed by the five raters. Each indicator of the PIPP-R is numerically rated on a Likert scale from 0 to 3 points, with higher ratings reflecting the rater’s impression of more intense pain responses. Additionally, the PIPP-R accounts for GA and baseline behavioral states as contextual factors. According to the instructions of the authors, these contextual factors need only be scored if there are changes in any of the behavioral or physiological items [26]. Neonates with the youngest GAs and those in quiet sleep receive the highest scores for these indicators. The PIPP-R scores will be used as a standard reference in this study.

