### Data analyses

Data will be analyzed using SPSS (IBM© SPSS© Statistics Version 23.0, IBM Corp, Armonk, NY, USA) and Stata (Stata/MP 13.1, StataCorp LP, [name], USA). Initially, an exploratory analysis will be conducted to describe the data and uncover any anomalies that may impact the validity of the data analysis. Methods for handling missing data will be applied after considering the volume and pattern of missing data. Descriptive statistics including measures of central tendency and dispersion will be used to characterize the individual variables and to determine the distribution of the data.

Several data analyses will be used for the validation of the BPSN. An exploratory factor analysis will be performed to analyze the underlying structure of the data. Cronbach’s Alpha and item-total correlations will be conducted to analyze the reliability of the scale. Furthermore, construct validity will be examined by comparing mean measurements at each of the three rated phases (baseline, heel stick and recovery). The analysis will be performed for the total sum score of the BPSN as well as for the physiological items and the behavioral items alone. In order to determine the concurrent validity of the BPSN with the PIPP-R, the total sum scores of the two tools will be correlated. Intra-class correlation (ICC) will be used to determine interrater reliability across the 2–5 heel sticks. To test sensitivity and specificity in the BPSN, a receiver operating characteristic (ROC) curve analysis will be performed using the PIPP-R as reference value. Furthermore, the pain and non-pain cut-off values of the two instruments will be compared.

To explore and depict both temporal variability of pain reactivity between measurements of each subject, and variability between corresponding measurements of all subjects, linear mixed modeling will be applied to the behavioral and physiological data on pain reactivity. Additionally, individual contextual factors will be added to these models to test for associations with the BPSN scores. As contextual factors are highly dependent on organizational procedures, the possible confounding effect of the participating sites will also be taken into account.

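### BPSN sensitivity and specificity are tested only against the PIPP-R, whose points for low GA and quiet sleep shift cut-off-based results in the youngest infants; a phase-referenced ROC should be added

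*Protocol article*

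**What the plan says.** All places are in the protocol article.

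- **Reference for the ROC (Data analyses).** Sensitivity and specificity of the BPSN come from one analysis: "a receiver operating characteristic (ROC) curve analysis will be performed using the PIPP-R as reference value". The same section adds that the pain and non-pain cut-offs of the two tools will be compared. It gives no PIPP-R cut-off and does not mention a PIPP-R score without contextual points.
- **Status of the PIPP-R (Measures).** "The PIPP-R scores will be used as a standard reference in this study".
- **PIPP-R scoring (Measures).** "Additionally, the PIPP-R accounts for GA and baseline behavioral states as contextual factors". On direction: "Neonates with the youngest GAs and those in quiet sleep receive the highest scores for these indicators". On the condition: "these contextual factors need only be scored if there are changes in any of the behavioral or physiological items".
- **BPSN scoring (The Bernese pain scale for neonates).** "Currently, the BPSN focuses entirely on physiological and behavioral indicators". A total of 11 or more indicates pain, whatever the GA.
- **Absence of a criterion (Pain assessment in neonates).** "no universally accepted gold standard exists for neonatal pain assessment".
- **Phase.** Each sequence belongs to a known phase (baseline, heel stick or recovery), and the raters are blinded to it. Data analyses uses phase to compare mean scores for construct validity, but does not name it as a reference for sensitivity and specificity.

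**The concern.** Sensitivity and specificity are meaningful only relative to the reference. Here the reference contains a term that depends on GA and not on what the infant does, and the index test has no such term. If the BPSN recorded reactions equally well at every GA, a fixed PIPP-R cut-off would still be reached with a smaller reaction in a 25-week infant than in a term infant. The BPSN at 11 would then seem to miss more pain in the younger infant.

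The study samples six GA groups and weights them towards the youngest. Infants below 30 weeks are 102/150 = 68% of the sample. If every preterm infant contributes five heel sticks, they supply up to 102 × 15 / 2106 = 72.6% of the sequences. A pooled sensitivity or a recommended cut-off would therefore mainly reflect infants for whom the reference threshold is effectively lowered. Whether one BPSN cut-off serves all GAs is the kind of question that readers will bring to these results.

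**Working it through.** The protocol article states no sensitivity, specificity, AUC or PIPP-R cut-off, so there is no figure to reproduce. The check starts from the scoring rules.

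**Step 1: direction.** Let S be the sum of the five PIPP-R behavioral and physiological items, g the GA points, c the PIPP-R cut-off and B the BPSN total. State points act in the same way as g. The contextual points count only when an item changes, so for S > 0 the reference is positive when S + g ≥ c, that is, when S ≥ c − g. Hence:

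- sensitivity = P(B ≥ 11 | S ≥ c − g)
- specificity = P(B < 11 | S < c − g), where sequences with S = 0 stay negative whenever c > 0.

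Giving g points is the same as lowering the cut-off on S by g. With B and S positively related, a lower threshold on S admits milder reactions as pain. Sensitivity falls and specificity rises.

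**Step 2: size, illustration A.** Assumptions:

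- identical reactions in every GA group
- B with mean 10, SD about 4.7, range 0–27
- S with mean 6, SD about 3.6, range 0–15
- correlation of B and S about 0.7
- g = 0 for term and 3 for the youngest, added only if S > 0. The 3 comes from reading "Each indicator of the PIPP-R is numerically rated on a Likert scale from 0 to 3 points" as covering the GA item too.
- 400,000 draws.

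| PIPP-R cut-off (assumed) | Sensitivity, g = 0 → 3 | Specificity, g = 0 → 3 | AUC, g = 0 → 3 |
|---|---|---|---|
| 6 | 0.68 → 0.53 | 0.82 → 0.94 | 0.828 → 0.854 |
| 7 | 0.73 → 0.57 | 0.76 → 0.91 | 0.828 → 0.841 |
| 8 | 0.79 → 0.62 | 0.71 → 0.86 | 0.832 → 0.833 |

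A rerun with the correlation set to 0.69 gave these figures to within about two points.

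**Step 3: size, illustration B.** This is built item by item: nine BPSN items and five PIPP-R items scored 0–3, the two physiological items shared, and 0–3 state points as well as GA points, all added only when S > 0. The distribution of reactions is again assumed, and equal across GA.

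| PIPP-R cut-off (assumed) | Sensitivity, g = 0 → 3 | Specificity, g = 0 → 3 | AUC, g = 0 → 3 |
|---|---|---|---|
| 5 | 0.66 → 0.49 | 0.99 → 1.00 | 0.951 → 0.939 |
| 7 | 0.82 → 0.58 | 0.95 → 0.995 | 0.967 → 0.935 |
| 9 | 0.93 → 0.74 | 0.88 → 0.97 | 0.972 → 0.960 |
| 11 | 0.98 → 0.88 | 0.80 → 0.92 | 0.972 → 0.970 |

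The identity in step 1 shows here: cut-off 7 with g = 2 gives 0.66 and 0.99, the same as cut-off 5 with g = 0. Fewer points give a smaller shift. At cut-off 7, g = 0, 1, 2, 3 gives sensitivity 0.82, 0.74, 0.66, 0.58.

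**Step 4: phase as reference (illustration B).** With equal reactions, BPSN sensitivity is about 0.90 and specificity about 0.96 at every g. If low-GA reactions are assumed to be damped by 20%, phase-referenced sensitivity falls to about 0.74. Against the PIPP-R at cut-off 7 with g = 3, sensitivity is 0.58 without damping and 0.50 with it, compared with 0.82 at g = 0 without damping. In this example most of the fall from 0.82 to 0.50 is present when reactions do not differ at all. The PIPP-R-referenced ROC alone cannot show how such a fall divides.

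**The case against.** Several counter-arguments have force.

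- **The GA question is answered elsewhere.** A reader might infer that the reference would manufacture the finding that GA should modify the BPSN. The documents do not support that. Contextual factors are tested in linear mixed models with BPSN scores as outcome, where the PIPP-R does not appear, and Study aims places the modification directly after the contextual-factor exploration. Nothing says that the ROC decides it. This stands.
- **The planned analysis is a ROC curve, and the AUC barely moves.** It changes by at most about 0.03 in either illustration, and in A it is equal or slightly higher with GA points. A claim that the BPSN would appear to discriminate worse in the youngest does not hold in general. The effect lies at fixed cut-offs. But the section names sensitivity, specificity and a cut-off comparison as outputs, so it is not empty.
- **No ROC by GA group is stated.** True. The article does not promise GA-specific sensitivities, so the distortion would enter through the pooled result or any later breakdown.
- **Equal reactions is the disputed assumption.** The background section on individual contextual factors says that premature infants' responses are less intense. GA points may then partly correct rather than distort. This stands, and it is why the planned ROC needs a companion.
- **Phase is used, and it is imperfect.** It serves the comparison of means. It marks the stimulus and not felt pain, and every infant receives sucrose. Comparison with an established scale is also a legitimate aim. These points speak against replacing the PIPP-R with phase as the main reference, but not against adding phase.

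**Conclusion.** The point holds in a limited form. As the only reference for BPSN sensitivity and specificity, the PIPP-R total lowers apparent sensitivity and raises apparent specificity at low GA when observed reactions are equal and cut-offs are fixed. The direction follows from the scoring rule in Measures and needs only a positive relation between the two scales.

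The size is illustrative. For 3 GA points, sensitivity falls by about 0.10 to 0.24 and specificity rises by about 0.01 to 0.15 across the cut-offs tried. These figures depend on the unstated PIPP-R cut-off, the 0–3 GA points, the reaction distributions and the correlation.

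The effect is confined to cut-off-based sensitivity and specificity and to the comparison of cut-offs. The AUC is little affected, and the mixed models not at all. GA points may partly correct for damped preterm responses, and the planned ROC cannot separate that from a scoring artefact. This is worth changing because the remedy is cheap, but it does not invalidate the validation study.

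**What to change.** 1. Keep the PIPP-R-referenced ROC as planned.
2. Add ROC curves of the BPSN and of the PIPP-R against the recorded phase (heel stick versus baseline), reported by GA stratum.
3. Repeat the PIPP-R-referenced ROC using the sum of the PIPP-R behavioral and physiological items, without GA and state points.
4. State that cut-off-based differences between GA groups will be interpreted from the three analyses together.

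Cost: a few sentences in the analysis section and some extra analysis. Phase is known for every sequence, the raters are already blinded to it, and the PIPP-R items are scored separately. The downside is that phase marks the stimulus rather than felt pain. With sucrose given to all infants, sensitivity against phase may look lower, so it should be read alongside the PIPP-R result and not in its place. The item sum in step 3 is not the PIPP-R as published and should be labelled as a sensitivity analysis.

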### Study aims

The aim of this observation study is the validation of the BPSN, using a large sample of neonates spanning a full range of GAs. The validation will involve the detection of the underlying structure of the data and the examination of the concurrent validity of the BPSN with the Premature Infant Pain Profile-Revised (PIPP-R; [26]), construct validity, interrater reliability, specificity and sensitivity. Furthermore, the variability of pain reactions over time related to behavioral and physiological patterns will be analyzed and the relationship between behavioral and physiological indicators examined. In addition, the influence of contextual factors on the variability of pain reactions across GA groups will be explored. Finally, the results of this analysis will be used for modification of the BPSN, to account for individual contextual factors in future clinical pain assessment in neonates.

Based on a previous validation study of the BPSN [41], we hypothesize that the BPSN will be a valid and reliable pain assessment tool for premature and term infants. In addition, we expect that the impact of single contextual factors on infants’ pain reaction will be described and considered for future pain assessment. In particular, we anticipate finding a difference in pain reaction depending on GA. Moreover, we hypothesize that behavioral and physiological indicators will show low association across time and that this low association may be explained by the influence of individual contextual factors.

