In addition to analyzing the total sum scores of the BPSN, the separate physiological and behavioral subscores will be tested both against the total scores and against one another. Pearson correlation will be used as a descriptive indication of the strength of associations, while linear mixed modeling will be used to test the associations themselves.

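### Testing each BPSN subscore against the total that contains it is a part-whole test: it is expected to be positive even when the two domains are unrelated (minor)

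*Protocol article*

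**What the plan says.** The Data analyses section closes with an analysis of the two BPSN domains. It begins "In addition to analyzing the total sum scores of the BPSN", so the total in question is the BPSN sum score, and goes on: "the separate physiological and behavioral subscores will be tested both against the total scores and against one another". The next sentence fixes the inferential role: "Pearson correlation will be used as a descriptive indication of the strength of associations, while linear mixed modeling will be used to test the associations". A corrected total, with the subscore removed, is not mentioned.

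The section on the Bernese scale gives the composition: "The BPSN is a 9-item multidimensional pain assessment tool that includes behavioral and physiological indicators". Seven items are subjective, and there are "two physiological (i.e. objective) (changes in heart rate and oxygen saturation) indicators". Every item scores 0 to 3.

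The hypothesis served is in Study aims: "we hypothesize that behavioral and physiological indicators will show low association across time".

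**The concern.** Each subscore is a component of the total it is tested against. Part of any association comes from the shared items, so the usual null of zero association does not describe unrelated domains. The size of the coefficient depends largely on how much of the total's variance each part contributes.

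What is at stake is interpretation. The article expects the two domains to be only weakly related. A significant p-value for each domain against the total, printed beside the between-domain result, could be taken as evidence that the domains belong together. It would carry no such evidence.

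**Working it through.** **Inputs.** From the article: 2 physiological and 7 subjective items, each scored 0-3, so the physiological subscore P runs 0-6 and the behavioural subscore B runs 0-21 (Bernese scale section); 150 infants and alpha 0.05 (Sample size and power); 134 preterm infants with 5 heel sticks and 16 term infants with 2 (Recruitment and data collection procedures). Assumed: a two-sided test, the seven subjective items forming the behavioural subscore, and the subscore SDs, which the article does not give. It states no figure for this analysis, so there is none to reproduce.

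**Slope.** With T = P + B,

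slope of T on P = Cov(P + B, P) / Var(P) = 1 + slope of B on P.

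The same holds in the mixed model. Writing T = a + bP + infant effect + error and subtracting P from both sides gives B = a + (b - 1)P + infant effect + error. It is the same model with the coefficient shifted by 1. Testing b = 0 therefore tests whether B falls by one point for each one-point rise in P, not whether B and P are unrelated. If the subscore is made the outcome instead, its slope on T at zero covariance is Var(P) / (Var(P) + Var(B)), which is also above zero.

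**Correlation.** With corr(P, B) = rho,

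r(P,T) = (sP + rho·sB) / sqrt(sP² + sB² + 2·rho·sP·sB), and at rho = 0, r(P,T) = sP / sqrt(sP² + sB²).

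Rejection at n = 150 is approximately Phi(atanh(r)·sqrt(147) - 1.96). For r = 0.275: 0.282 × 12.12 = 3.42; 3.42 - 1.96 = 1.46; Phi = 0.928.

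| Assumption, with rho = 0 | r(P,T) | r(B,T) | Rejection, P against T |
|---|---|---|---|
| Nine equal, uncorrelated items: variances 2 and 7 | 0.47 | 0.88 | about 100% |
| Behavioural items correlated at 0.4: variances 2 and 7 + 42 × 0.4 = 23.8 | 0.28 | 0.96 | about 93% |
| SDs proportional to score range, 6:21 | 0.275 | 0.962 | 92.8% |
| Six behavioural items, 6:18 | 0.316 | 0.949 | 97.8% |
| Equal SDs | 0.707 | 0.707 | about 100% |
| Extreme SD ratio, 1:6 | 0.164 | 0.986 | 52.1% |

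B against T rejects about 100% of the time in every row. The six-item row is there because Measures counts six subjective indicators but lists seven; the conclusion is the same.

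**Simulated 0-3 items**, one observation per infant, 3,000 runs, domains independent: r(P,T) = 0.296 with 95.7% rejected; r(B,T) = 0.955 with 100% rejected; r(P,B) = 0.00 with 5.3% rejected.

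**Simulated mixed models** with a random intercept, 134 × 5 + 16 × 2 = 702 observations, assumed intraclass correlation 0.3, and 150 runs for each of two SD ratios (6:21 and sqrt 2 : sqrt 7):
- T on P: slope 1.00, 100% rejected.
- T on B: slope 1.00, 100% rejected.
- B on P: slope 0.00, 4.7% and 5.3% rejected, consistent with the nominal 5%.

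**When the overlap cancels.** r(P,T) is zero at rho = -sP/sB. At 6:21 this is -6/21 = -0.29. For the behavioural part the corresponding value is -21/6, which no correlation can reach.

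**The case against.** The strongest defence is that the quoted sentence already contains the right test. Subscore against subscore has no overlap, holds its nominal size in simulation, and answers the Study aims hypothesis. That stands. A reader might infer that the hypothesis test itself is compromised; it is not. The sample size, ROC analysis, ICC, factor analysis and phase comparisons are likewise untouched.

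A reader might also infer that these tests decide which items survive in a revised scale. The article does not say so. Study aims ties the revision to contextual factors, and item structure is examined separately by factor analysis, Cronbach's alpha and item-total correlations.

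Nor is it right that both associations come out strong and significant whatever the truth. The physiological correlation is modest (about 0.28 in one scenario), disappears at a between-subscore correlation near -0.29, and is detected only about half the time at the 1:6 ratio with single observations. Item counts alone do not set it either: with 2 and 7 items fixed, r(P,T) moves from 0.47 to 0.28 as the behavioural items become correlated.

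Finally, a part-total correlation has a fair descriptive use, showing how far each domain drives the total, and the article does label Pearson correlation descriptive. That stands for the correlation. It does not cover the mixed model, which is named as the test.

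**Conclusion.** The point holds, at minor severity. The subscore-total mixed models test a null that does not correspond to unrelated domains, so their p-values say nothing useful about coherence. The slope result is exact algebra and needs no assumption beyond the total being the sum of its two parts. The correlations and rejection rates are illustrations: they rest on assumed subscore variances, a two-sided 5% level and, for the mixed models, an intraclass correlation of 0.3 and the article's full heel-stick counts. The damage is confined to how these particular tests might be read.

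**What to change.** Amend the one sentence. Either delete the inferential tests of each subscore against the total, or replace the total with the total minus the subscore. With only two subscores the second option is the between-subscore model already planned, so nothing informative is lost. Any subscore-total correlation that is kept should be described as a part-whole figure and given without a p-value. Report the between-subscore coefficient with its 95% confidence interval, so that a low association is judged from the range of values compatible with the data and not from non-significance. The cost is one line of analysis text, with no new data and no change to the sample size.
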